## Methods and Analysis

### Design

This study is an observational prospective cohort study focused on identifying pre-procedural risk factors for the development of delirium and cognitive decline following TAVI. Potential risk factors will be measured prior to TAVI (baseline). Cognitive function, activities of daily living, quality of life, and mortality outcomes will be assessed at 3-, 6-, and 12-months post-operatively. Delirium presence will be measured on each of the first 2 days following TAVI.

### Setting

Recruitment of participants occurs at one site: The Royal Adelaide Hospital. The Royal Adelaide Hospital is a public hospital located in the central business district of Adelaide, Australia. Delirium assessments (days one and two post-TAVI) are conducted where the participant is located on that day; in hospital or at their home (if they have been discharged). Baseline and follow-up testing sessions at 3-, 6-, and 12-months post-TAVI are conducted in participants' homes.

Recruitment commenced in May 2018 and is currently underway. The rate of recruitment is ~20 participants per year. However, the study was placed on hold for a significant portion of 2020 due to COVID-19 restrictions. To ensure fulfillment of the required sample size (*n* = 60, see Sample Size section), active recruitment is anticipated to continue until December 2021 (3.5 years in total), with study completion (end of 12-month follow-ups) in December 2022.

### Selection of Subjects

#### Inclusion Criteria

Participants are eligible if they are aged 60 years and over and have consented to undergo an elective TAVI procedure at the Royal Adelaide Hospital. They must live within a 1-h drive of the central business district of Adelaide. Normal hearing (with or without the use of aids) and proficient English language are also required. People with a clinical diagnosis of a neurodegenerative condition (including dementia) are also eligible for inclusion to reflect the general older population undergoing cardiovascular procedures. A different consent process, where a person responsible provides written and verbal consent, is undertaken for those with such diagnoses.

#### Exclusion Criteria

Participants will be ineligible for inclusion if they have: current or recent (within the past year) alcohol or substance abuse or dependence; recently (past month) used recreational drugs; a diagnosed learning disability; any conditions not typically associated with ischemic heart disease and likely to affect mobility, voice or swallowing to a significant degree (including congenital conditions, structural abnormalities, or cancer in pertinent regions of the body); already enrolled in a TAVI clinical trial; severe visual impairment.

### Sample Size

We want to capture any relationships between risk factors and cognitive outcomes which have potential clinical utility. As such, to detect a medium-large effect size or higher (*r* ≥ 0.4), with power = 0.8, α = 0.05, we computed [using G^*^Power statistical analysis software (54)] that a sample size of 44 is required. To account for attrition, a total of 60 participants will be recruited.

### Honoraria

Participants will receive a total of AUD$80 (4 × $20) worth of vouchers across the duration of the study to cover time and other costs associated with participation. One voucher is supplied to participants after the completion of the pre-TAVI baseline as well as after 3-, 6-, and 12-month post-TAVI follow-up sessions.

### Measures

#### Primary Outcomes

##### Cognitive Decline

Addenbrooke's Cognitive Examination III (ACE-III) will be used to identify cognitive decline. The ACE-III is a measure of global cognition, widely used as a dementia screening tool. It comprises five cognitive domains: attention, memory, verbal fluency, language, and visuospatial abilities. Possible scores range from 0 to 100, with higher scores representing better cognition. High sensitivity and specificity are found for the two suggested cut-offs, of 88 for MCI (sensitivity = 1.0, specificity = 0.96) and 82 for dementia (sensitivity = 0.92, specificity = 1.0) (55). The ACE-III also demonstrates good internal reliability (α = 0.88) and has three parallel versions which are all used within the study to allow for longitudinal cognitive testing (55). ACE-III version A will be used at baseline and 12-month follow-up, version B at 3-month follow-up, and version C at 6-month follow-up. The ACE-III score will be used to characterize participants as with or without cognitive decline (compared to baseline) at each follow-up timepoint (3-, 6-, and 12-months post-TAVI). Cognitive decline will be defined in the present study as a decline (from baseline to follow-up) of 4 or more points in ACE-III score. As an effect-finding study, this cut-off was chosen to weight toward false positives, and was based on one standard deviation (3.3) in ACE-III score previously reported for older adults (56).

##### Delirium

The presence of delirium will be assessed using the Confusion Assessment Method for the Intensive Care Unit (CAM-ICU) (57) for those in the ICU or the CAM (58) for participants in non-ICU wards or who have been discharged home. The CAM-ICU-7 (59) will be calculated to quantify delirium severity in the ICU. For participants in non-ICU wards or at home, the Memorial Delirium Assessment Scale (MDAS) (60) interview will be conducted to inform the scoring of the CAM and as a measure of delirium severity. The CAM and CAM-ICU comprise four main features of delirium: (1) acute onset and fluctuating course; (2) inattention; (3) disorganized thinking; and (4) altered level of consciousness. Altered level of consciousness will be assessed using the Observational Scale of Level of Arousal for the CAM, and the Richmond Agitation and Sedation Scale for the CAM-ICU. We define a positive diagnosis of delirium as the presence of features 1 and 2 and either 3 or 4 on the CAM or CAM-ICU. For any positive delirium diagnoses the delirium motor subtype (hypoactive, hyperactive, mixed, no subtype) will also be evaluated using a checklist by Meagher (61). Presence of delirium was considered as a positive diagnosis on either days 1 or 2 post-TAVI. All research team members conducting delirium assessments will be trained by qualified geriatricians ([name]).

#### Secondary Outcomes

##### Cognition (Continuous)

In addition to the dichotomous primary outcome of cognitive decline, change in cognition from baseline to each follow-up will be evaluated as a continuous secondary outcome. This change will be represented by *z*-score of the cognitive change score calculated for each follow-up timepoint in our sample (difference between an individual's score at follow-up and score at baseline). Change in ACE-III score, as well as change on tests conducted using Cambridge Neuropsychological Test Automated Battery (CANTAB) will be considered. A three-test battery will be run using the portable CANTAB testing system. The tests employed will be the Motor Orientation Task (MOT), Reaction Time (RTI), and Pattern Recognition Memory (PRM). The MOT will be used purely as tablet familiarization and, as such, no data will be analyzed from this task. Memory and attention are cognitive domains in which acute impairments are found following valve replacement (62). CANTAB allows for detection of changes in these more specific domains, rather than global cognition (ACE-III), with RTI primarily as a measure of attention and PRM primarily for visual memory. RTI and PRM provide multiple outcome measures. For both, a z-score for change (from baseline to follow-up) in each relevant outcome (e.g., reaction time, errors) will be calculated and then averaged, creating a composite z-score outcome for each test.

##### Additional Secondary Outcomes

Secondary outcomes also comprise quality of life and activities of daily living, which are measured using the EuroQol-5D (63) and Barthel Index of Activities of Daily Living (64), respectively, at 3-, 6-, and 12-months after TAVI. Mortality was also recorded as a secondary outcome at the same three timepoints post-procedure.

#### Potential Risk Factors

All potential factors to be measured are presented in Table 2, along with their duration and the time-points of the study at which they are assessed.

**Table 2 T2:** Measures and assessments utilized throughout study period, with approximate collection time.

**Assessments**	**Duration (min)**	**Baseline**	**D1**	**D2**	**3 M**	**6 M**	**12 M**
**Cognitive Battery**							
Addenbrooke's Cognitive Examination-III (ACE-III) (56)^*^	15	X			X	X	X
Motor Screening Task (CANTAB)^*^	2	X			X	X	X
Reaction Time (CANTAB)^*^	3	X			X	X	X
Pattern Recognition Memory (CANTAB)^*^	5	X			X	X	X
**Delirium Daily Screen**							
Memorial Delirium Assessment Scale (MDAS)^*^ (60)	15		X	X			
Confusion Assessment Method Short Form (CAM) (58) or CAM-ICU (57) [and CAM-ICU-7 (59)]	3-5		X	X			
Motor Subtype Classification (61)	1		X	X			
**Activities of Daily Living**							
Barthel Index of Activities of Daily Living (64)	5	X			X	X	X
**Quality of Life**							
EuroQol-5D (63)		X			X	X	X
EuroQol-VAS (63)		X			X	X	X
**Mortality**							
**Electroencephalography**							
Resting Data (Note: related to a sub-study, not discussed further here)	30	X					
**Mood and Behavior**							
Geriatric Depression Scale (GDS) (65)	3	X					
Neuropsychiatric Inventory Questionnaire (NPI-Q) (66)	5	X					
Insomnia (Hamilton Rating Scale for Depression) (67)	2	X					
**Gait**							
Single-task gait speed		X					
Dual-task gait speed		X					
Dual-task gait cost		X					
Step length		X					
**Visual Symptoms**	10						
Diplopia		X					
Blink rate		X					
**Voice pitch**	5						
Pitch minimum		X					
Pitch maximum		X					
Pitch range		X					
Average pitch		X					
**Dysphagia**	1						
Sydney Swallowing Questionnaire (68)		X					
**Frailty**	5						
Edmonton Frail Scale (69)		X					
**Additional Measures**							
Saliva sample (APOE4 allele)	5	X					
**Medical History**	NA^*†*^						
Renal disease		X					
Previous stroke/TIA		X					
Atrial fibrillation		X					
Coronary artery disease		X					
Hypertension		X					
Peripheral vascular disease		X					
**Risk Scores**	NA^*†*^						
EuroSCORE II		X					
Society of Thoracic Surgery		X					
**Procedural Factors**	NA^*†*^						
Valve access type			X				
Procedure time			X				
**Population Characteristics**	NA						
Age		X					
Gender		X					
Height		X					
Weight		X					
Body mass index		X					
**Population Characteristics (collected at baseline)**	5						
Waist circumference		X					
Years in education		X					
Social engagement		X					
Physical activity		X					
**Approximate session durations (minutes)**		120	20	20	45	45	45

*CANTAB, Cambridge Neuropsychological Test Automated Battery; D1, day 1 post-TAVI; D2, day 2 post-TAVI; 3 M, 3-months post-TAVI; 6 M, 6-months post-TAVI; 12 M, 12-months post-TAVI; NA, Not applicable; TIA, transient ischemic attack*.

* *This assessment has parallel versions (or randomized aspects) to be used in follow-up sessions*.

† *Assessments are conducted/collected by the Royal Adelaide Hospital (administration, nursing staff and doctors) in the lead up to TAVI and during hospital stay, all other assessments to be conducted by researcher*.

##### Depression

The Geriatric Depression Scale (GDS), developed to detect level of depression in older populations (65), will be used to assess depression. The GDS consists of 15 items with response options of yes or no (i.e., “Are you in good spirits most of the time?”). Possible scores range from 0 to 15, with higher scores indicating greater likelihood of depression. Compared with diagnostic criteria, the GDS has high sensitivity (92%) and specificity (89%) (65).

##### Neuropsychiatric Symptoms

Neuropsychiatric symptoms will be evaluated using the Neuropsychiatric Inventory Questionnaire (NPI-Q) (66). This questionnaire is designed to be completed by the caregiver of a person with dementia. The caregiver is asked to note whether each of 12 neuropsychiatric symptoms (e.g., apathy/indifference, appetite/eating disturbances) have been present in the patient within the past month. If a symptom has been present, they then rate both the severity of the symptom (from 1 to 3, with higher scores indicating greater severity) and the distress it causes them (from 0 to 5, with higher scores indicating greater distress) (66). In this study, a family member or spouse of the participant will complete the NPI-Q. The person completing the NPI-Q must be without a clinical diagnosis of dementia, have sufficient English language and normal or corrected-to-normal vision (to ensure accuracy of report).

##### Insomnia

Insomnia will be assessed using the early, middle, and late insomnia items of the Hamilton Rating Scale for Depression (67). Each of these items is rated on a scale which ranges from 0 (absent) to 2 (severe). These early, middle and late insomnia items have been found to correlate highly (Spearman rho = 0.63, 0.49, and 0.49, respectively) with weekly averages for respective items measured using a sleep diary (70).

##### Gait

The assessment of gait will include single-task gait speed, dual-task gait speed, dual-task gait cost and step length. Each task will involve walking 6 meters, with participants able to use a walking aid if needed. Single-task gait speed is calculated as the distance (6 meters) divided by the time taken to walk the distance (in seconds). Dual-task gait speed is calculated in the same way as single-task gait speed, except participants count backwards from 100 (i.e., “100, 99, 98…”) while performing the walking task. Dual-task gait cost is calculated in the following way:

$$\begin{array}{l} \text{Dual task gait cost}=\frac{\text{Single task gait speed}-\text{Dual task gait speed}}{\text{Single task gait speed}}\\ \;\times 100 \end{array}$$

Step length (in cm) is calculated as the distance (600 cm) divided by the number of steps taken during the single-task gait assessment.

##### Diplopia

A protocol to assess presence of diplopia using an eye cover test was developed in discussion with a neuro-ophthalmologist. Participants' best corrected visual acuity (BCVA) will be assessed using a Snellen eye chart placed 6 meters away. A fixation letter which is 2 lines above the BCVA of a participant's worst eye will be chosen, and participants will be instructed to fixate on this throughout the eye cover test. The eye cover test will begin with the right eye being covered and then uncovered several times (holding for 1 s in each position), while watching the left eye for movement. The same process is then undertaken on the opposite eye. An alternating cover test is then performed, moving the occlude between the right and left eye (holding for 1 s over each) and watching for movement in either eye. Presence of double vision or blurry vision (by self-report) in addition to any eye movements (in right or left eye) during the eye cover task will be counted as presence of diplopia.

##### Blink Rate

The protocol for assessing eye blink rate was modeled based on the conversation task of Fitzpatrick et al. (49). Participants will be video recorded during 2 min of free speech, with prompts from the researcher only if needed. The average number of blinks per minute will be calculated from 3 separate trials of 20 s each from the 2-min recording. A blink is considered eye closure of at least 50%. Blink rate will be split into three equal groups for analyses, with middle being compared to low and high blink rate, in case of a non-linear relationship.

##### Voice

Measures of voice pitch (maximum, minimum, range and average) in Hz will be taken during sustained phonation /a/ at a comfortable pitch for the participant. Results will be based on an average taken from three separate recordings of 5 s duration each. All recordings used for average calculations will be free of background noise. The VoiceAnalyst app (iOS/Apple) will be used on an iPad (with microphone placed 20 cm away from participants' mouths) to take recordings and measure voice pitch. Male and female voice data will be analyzed separately.

##### Dysphagia (Difficulty Swallowing)

To assess difficulty swallowing, participants will be asked to respond to the question “Do you have any difficulty swallowing your saliva?” using a 10 cm visual analog scale, ranging from “No difficulty at all” (0 cm) to “Unable to swallow at all” (10 cm). This question was taken from the Sydney Swallowing Questionnaire (68).

##### Frailty

Frailty will be assessed using the Edmonton Frail Scale (69). This is a clinician-administered measure which comprises 10 domains. Some domains are assessed with performance-based items (e.g., the Clock Test for cognitive impairment), and others are quantified using questions with defined responses (e.g., “Do you use five or more prescription medications on a regular basis?” for medication use). Possible scores range from 0 to 17, with higher scores representing higher levels of frailty. The Edmonton Frail Scale has demonstrated good inter-rater reliability (κ = 0.77) and internal consistency (α = 0.62) (69). The Edmonton Frail Scale is also significantly correlated (*r* = 0.64) with the Geriatrician's Clinical Impression of Frailty (69).

##### APOE4 Allele

A saliva sample will be taken using an Oragene kit to test for presence or absence of the apolipoprotein E4 (APOE4) allele.

##### Medical History and Procedural Factors

Pertinent medical history, risk scores and procedural factors (see Table 2), based on those identified through previous research, will be collected from Royal Adelaide Hospital records.

#### Sample Characteristic Data

##### Population Characteristics

General population characteristics will also be collected in order to characterize the sample. These measures include age, gender, years in education (including primary, secondary and any further formal education), height, waist circumference, weight, and body mass index. Level of social engagement and physical activity will be collected by self-reported rating of the frequency participants see a member of their family or friend and take part in physical activity. Response options for these self-reports are daily, weekly, fortnightly, monthly, less than monthly, and never.

### Procedure

The study timeline is outlined in Figure 1. Potential participants are approached in-hospital following the pre-procedural consult for their TAVI procedure. This typically occurs 1–4 weeks pre-TAVI. Informed consent is obtained from eligible and interested participants. Consenting participants then complete a baseline testing session (~2-h duration) in their home prior to their TAVI procedure. Multiple assessments (outlined in Table 2) are conducted at this baseline session. Prior to their procedure, a researcher also reviews the hospital medical history records for the participant to obtain relevant medical history data (see Table 2).

**Figure 1 F1:**

Study timeline showing pre-TAVI baseline as well as post-TAVI delirium assessment and three follow-ups. B, baseline; D, delirium assessment; F, follow-up.

On the 2 days following their TAVI procedure, participants are assessed for delirium. This occurs either in-hospital or at their home, based on their location that day and if they have been discharged from hospital. A researcher also reviews the participant's medical record from the Royal Adelaide Hospital's records to obtain TAVI procedure information (see Table 2).

Participants are then contacted again at 3-, 6-, and 12-months post-TAVI to arrange follow-ups (~45-min duration). These sessions are once again conducted in participant's homes. If participants are unable to be contacted for follow-up, their next of kin is contacted.

### Data Analysis

To determine the relationship between the potential risk factors measured within this study and outcomes (primary and secondary), a series of univariate logistic and linear regressions will be conducted. Each predictor will be entered into a separate model for each primary outcome: presence vs. absence of delirium post-TAVI, as well as presence vs. absence or cognitive decline. The same will be done for secondary outcomes: cognition, mortality, quality of life, and activities of daily living at each follow-up (3-, 6-, and 12-months post-TAVI). Logistic regressions will be run for categorical outcomes (cognitive decline, delirium, and mortality) and linear regressions will be run for continuous outcomes (cognition, quality of life, activities of daily living). As this is an exploratory, effect-finding study, we will not correct for multiple comparisons and multivariable models will not be run. The purpose of this study is to propose variables to be taken forward into independent and larger samples, to develop TAVI-specific risk prediction tools for delirium and cognitive decline.

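### Quality of life and daily living appear to be modelled as follow-up levels without their baseline scores, so these secondary results cannot separate pre-TAVI status from the course after TAVI.

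*Protocol article*

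**What the plan says.** All references are to the protocol article.

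- **Data Analysis** enters each predictor in its own model for the primary outcomes and then extends this: "The same will be done for secondary outcomes: cognition, mortality, quality of life, and activities of daily living at each follow-up". Linear regression is used for quality of life and activities of daily living. The section adds: "we will not correct for multiple comparisons and multivariable models will not be run".
- **Additional Secondary Outcomes** introduces the two measures with "Secondary outcomes also comprise quality of life and activities of daily living" and places them at 3, 6 and 12 months. It defines no change score.
- **Table 2** marks the row "Barthel Index of Activities of Daily Living (64") at baseline and at all three follow-ups. The EuroQol-5D and EuroQol-VAS rows are marked the same way.
- **Cognitive Decline** and **Cognition (Continuous)** both refer the ACE-III to its baseline value, the first as a drop of 4 or more points and the second as a z-scored change.

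The article gives no reason for treating quality of life and daily living differently from cognition.

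**The concern.** The candidate predictors are measured before TAVI, most of them at the same home visit as the baseline Barthel and EuroQol. Frailty, gait and mood may well be related to function and quality of life on that day. The Introduction itself cites a link between impaired mobility and reduced quality of life in TAVI populations. If a person's scores persist over the following year, such a predictor will correlate with the follow-up level even when it carries no information about what happens after the procedure.

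A single-predictor model on the follow-up level cannot tell these two situations apart. What is at stake is the reading of the secondary results: a measure could be described as foreshadowing poor function or quality of life after TAVI when it only records that the patient already had it. Replication in a larger sample would not correct this, because the association is systematic and not due to chance.

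**Working it through.** **1. The plan's own figure.** Inputs from Sample Size: "to detect a medium-large effect size or higher (*r* ≥ 0.4"), "with power = 0.8, α = 0.05", and "that a sample size of 44 is required". Sidedness is not stated. For a two-sided t test of a slope, noncentrality = r/√(1 − r²) × √n with n − 2 degrees of freedom. At r = 0.4, power is 0.798 for n = 43 and 0.807 for n = 44. The stated 44 reproduces, so the sample size is not in dispute, and the same formula is used below.

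**2. Set-up.** Let a be the correlation of the predictor with the baseline score and b the correlation of baseline with follow-up. Suppose the predictor has no association with follow-up once baseline is known. Its unadjusted correlation with the follow-up level is then a × b. The document gives neither a nor b, so all values here are assumptions.

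**3. Chance of p < 0.05 in the planned model, n = 44.**

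| a | b | a × b | Noncentrality | Significant |
|---|---|---|---|---|
| 0.3 | 0.5 | 0.15 | 1.01 | 17% |
| 0.5 | 0.6 | 0.30 | 2.09 | 53% |
| 0.5 | 0.7 | 0.35 | 2.48 | 68% |

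A simulation with 20,000 replicates per setting agrees closely: 16.3%, 51.6% and 66.3%. Over a wider grid (a from 0.2 to 0.6, b from 0.5 to 0.8) it runs from 9.8% to 92.7%. With a = 0.5 and b = 0.8 the product is 0.40, exactly the effect the study is powered to detect.

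**4. With baseline as a covariate.** In the same simulation the rate is about 5% in every setting (4.7% to 5.3%, at n = 44 and n = 60).

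**5. Would a change score do instead?** Not fully. Follow-up minus baseline still flags such predictors in 6.7% to 52.5% of analyses at n = 44, because of regression to the mean (equal variances at the two times assumed).

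**6. Does adjustment also buy precision?** Not in general. The ratio of adjusted to unadjusted slope variance, leaving aside the lost degree of freedom, is (1 − b²) / [(1 − a²)(1 − a²b²)].

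- a = 0.3, b = 0.5: 0.75 / (0.91 × 0.9775) = 0.84
- a = 0.5, b = 0.6: 0.64 / (0.75 × 0.91) = 0.94
- a = 0.5, b = 0.7: 0.51 / (0.75 × 0.8775) = 0.78
- a = 0.5, b = 0.5: 0.75 / (0.75 × 0.9375) = 1.07
- a = 0.6, b = 0.6: 0.64 / (0.64 × 0.8704) = 1.15

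Baseline reduces residual variance, but collinearity between predictor and baseline takes some or all of the gain back.

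**The case against.** **The unadjusted association is not an error.** Under the assumptions above the correlation with follow-up level really is a × b, so rejecting zero is correct for the hypothesis the planned model tests. A pre-procedural measure associated with the 12-month level is informative for predicting that level. This stands. The 17% to 68% are not false-positive rates for the planned test; they show how often a predictor with nothing to add beyond baseline would still be flagged.

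**The study's aim lies elsewhere.** The end of the Introduction and Data Analysis both direct the work to risk models for delirium and cognitive decline. A reader might infer that the study's central question is compromised. The document does not support that: delirium is assessed on days 1 and 2, cognitive decline is already referred to baseline, and no stated aim carries variables forward for quality of life or daily living.

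**The level reading is inferred.** The quoted sentence also covers cognition, which is defined elsewhere as change, so its wording alone does not settle the point. Outcome coding might sit in a fuller document. But with change defined explicitly for cognition and not for these two outcomes, level is the natural reading. The bar on multivariable models, moreover, is stated outright and excludes baseline as a covariate.

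**The study is declared exploratory.** That justifies tolerating chance findings and limits the harm. It does not address a systematic association through baseline status.

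A reader might also infer that such factors certainly will be reported as predictors, or that adjustment must sharpen the estimates. Neither follows: the first depends on unknown correlations, and the second can reverse (step 6).

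**Conclusion.** The point holds for the secondary outcomes of quality of life and activities of daily living only. As written, these models describe association with the follow-up level and cannot be read as information about the course after TAVI.

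The size rests on assumed correlations, a linear model and n = 44. A predictor with no association given baseline would be significant in about 17% to 68% of analyses across the settings tabulated, against 5% with baseline included. Predictors unrelated to the baseline scores stay at 5% either way. No general gain in precision should be claimed. It is a modest point, worth correcting because the data are already scheduled and the protocol's own rule blocks the remedy.

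**What to change.** Amend Data Analysis as follows:

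- In every EuroQol-5D, EuroQol-VAS and Barthel model, enter the participant's own baseline score on that measure alongside the single predictor.
- State that this is an exception to the rule against multivariable models.
- Keep the unadjusted estimate, labelled as a descriptive association with follow-up level.
- Interpret only the baseline-adjusted estimate as prediction of outcome beyond pre-TAVI status.

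A change score should not be substituted, for the reason in step 5.

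The cost is a few sentences, one degree of freedom per model, and some collinearity where a predictor is closely related to the baseline score. No new data are needed.

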In summary, this study will investigate associations between a wide range of factors and post-TAVI delirium and cognitive decline. Existing risk scores (STS and EuroSCORE), factors incorporated within current delirium risk prediction tools, and factors with reported associations to post-operative delirium will be evaluated. In addition to this, we will include a range of novel measures which are drawn from the literature of aging and frailty. The aim of this effect-finding study is to identify potential measures from which to develop risk prediction models for cognitive decline (at 3-, 6-, and 12-months post-procedure) and delirium specifically for TAVI patients. Such risk prediction models will aid in the identification of at-risk patients, allowing for earlier and targeted intervention to reduce the occurrence of delirium and cognitive decline following these procedures.

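### Continuous outcomes are regressed visit by visit, so each fit ignores the participant's other visits; one repeated-measures model per predictor would protect later-visit slopes if dropout follows earlier scores.

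*Protocol article*

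**What the plan says.** The Data Analysis section states that "a series of univariate logistic and linear regressions will be conducted", with each predictor in its own model. Secondary outcomes are handled the same way: "cognition, mortality, quality of life, and activities of daily living at each follow-up (3-, 6-, and 12-months post-TAVI". For the model type, it says "linear regressions will be run for continuous outcomes (cognition, quality of life, activities of daily living". No model that joins the three visits is named.

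The Cognition (Continuous) section fits this reading: change is expressed as a z-score "of the cognitive change score calculated for each follow-up timepoint in our sample". Binary decline, a primary outcome, is also classified visit by visit: "The ACE-III score will be used to characterize participants as with or without cognitive decline (compared to baseline) at each follow-up timepoint".

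Three other statements bear on the point:

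- Sample Size derives 44 participants and then says "To account for attrition, a total of 60 participants will be recruited".
- The closing paragraph of the Introduction sets the aim as finding measures for "risk prediction models for cognitive decline (at 3-, 6-, and 12-months post-procedure) and delirium specifically for TAVI patients".
- Data Analysis calls the study exploratory and says "we will not correct for multiple comparisons and multivariable models will not be run".

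The article does not say how missed visits are handled.

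**The concern.** Each continuous outcome is measured at baseline and three times after the procedure, but each regression sees one follow-up only. An ordinary linear regression at 12 months can use only people with a 12-month score; what is known about the others from 3 and 6 months plays no part.

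That matters if people who scored worse at 3 or 6 months are less likely to be seen later. The 12-month fit then rests on a sample selected on something related to the outcome, and having the predictor in the model does not remove the selection. The slope usually shrinks. The study exists to choose variables to carry forward, so a useful predictor could be passed over at the later visits.

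**Working it through.** **1. The plan's own figure.** Inputs from Sample Size: r = 0.4, power 0.80, alpha 0.05. For one single-predictor regression, the noncentrality is r/sqrt(1 - r²) × sqrt(N) with N - 2 degrees of freedom. At N = 44 this is 0.4/sqrt(0.84) × sqrt(44) = 2.89. Two-sided power is 0.807 at N = 44 and 0.798 at N = 43, so 44 is reproduced. It is the size for one regression at one visit. The attrition allowance is 1 - 44/60 = 26.7%. A single-visit fit therefore keeps its stated power if losses stay within that allowance. What remains is who those 44 are and what the unused visits could add.

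**2. Assumptions the article does not supply.** Between-visit residual correlation: 0.5, 0.7 and 0.9. Dropout: monotone, logistic in the predictor (coefficient 0.7) and the previous visit's outcome (coefficient 0, 0.7 or 1.5, here called none, moderate and strong). The labels are conventions, not estimates.

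**3. Simulation at the plan's effect size.** N = 60, true slope 0.40 at every visit, 4,000 runs per setting. The 12-month least-squares fit in those observed is compared with a likelihood estimate of the same 12-month slope from all visits. Empirical standard errors are in brackets.

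| Correlation | Dependence on earlier score | 12-month fit alone | All visits |
|---|---|---|---|
| 0.5 | none | 0.401 (0.156) | 0.402 (0.151) |
| 0.7 | none | 0.401 (0.157) | 0.399 (0.147) |
| 0.9 | none | 0.402 (0.152) | 0.402 (0.137) |
| 0.5 | moderate | 0.362 | 0.404 |
| 0.7 | moderate | 0.339 | 0.397 |
| 0.9 | moderate | 0.326 | 0.400 |
| 0.5 | strong | 0.308 | 0.399 |
| 0.7 | strong | 0.276 | 0.398 |
| 0.9 | strong | 0.254 | 0.403 |

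Retention at 12 months was 63-72%, slightly below the plan's 44/60 = 73%.

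- *Dropout on the predictor only:* no bias. The standard error falls by 1 - 0.151/0.156 = 3%, 1 - 0.147/0.157 = 6% and 1 - 0.137/0.152 = 10%.
- *Dropout on the earlier score:* the single-visit slope falls to 0.33-0.36 (moderate) or 0.25-0.31 (strong); the all-visit estimate stays at 0.40.

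**4. Simulation with retention nearer the plan's.** N = 60, about 45 left at 12 months (75%), true slope -0.30, correlation 0.5-0.7. The joint model has a predictor-by-visit term, so both columns estimate the same 12-month slope.

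| Dropout | Separate slope | Joint slope | Power, separate | Power, joint |
|---|---|---|---|---|
| unrelated to scores | unbiased | unbiased | about 0.54 | 0.56-0.59 |
| moderate dependence | -0.25 to -0.26 | about -0.30 | 0.39-0.41 | 0.53-0.57 |
| strong dependence | -0.16 to -0.20 | about -0.30 | 0.18-0.25 | 0.47-0.53 |

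The attenuation is (0.30 - 0.26)/0.30 = 13% to (0.30 - 0.25)/0.30 = 17% under moderate dependence, and (0.30 - 0.20)/0.30 = 33% to (0.30 - 0.16)/0.30 = 47% under strong. A milder setting also labelled moderate (correlation 0.6) gave -0.28, a 7% attenuation, so the size depends heavily on the assumed mechanism.

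**The case against.** The strongest reply is that single-predictor, single-visit screening is a declared and coherent choice. The aim is visit-specific, the sample size fits one regression at one visit, most of the outcomes affected are secondary, and promising variables go on to larger samples. Nothing in the text is contradictory. The article also gives no missing-data rule, and such a rule may sit in an analysis plan not shown. All of this stands and limits the weight of the point. It does not remove it: the model is stated, the exploratory rationale covers multiplicity and multivariable models and gives no reason to analyse visits apart, and a predictor-by-visit term keeps the visit-specific aim.

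Four stronger readings are tempting, and the documents do not support them:

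- *Large loss of power.* A visit-averaged slope at N = 44 with complete data would have power 0.83-0.97 (correlations 0.9 to 0.3) against 0.807 for one visit. That is a different quantity and assumes equal effects at all visits. For a visit-specific slope, with dropout unrelated to scores, the gain is small.
- *Associations necessarily biased toward survivors.* Loss of frail participants does not by itself bias the frailty model, because frailty is in it. Bias needs dependence on earlier scores beyond the predictor, and the article gives no dropout mechanism. Nor does a mixed model answer selection by death, since scores after death are undefined.
- *Three tests per predictor as a multiplicity fault.* The plan openly declines correction, and the joint model still reports three slopes.
- *The same result for the primary binary outcome.* Decline is also classified at each visit, but the figures above are for continuous outcomes. Unweighted GEE would not cure outcome-dependent dropout.

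**Conclusion.** The point holds in a limited form: a cheap improvement, not an error. Fitting the continuous outcomes one visit at a time sets aside information already collected. If living participants miss later visits because of earlier scores, the 12-month slope can shrink by about 13-17% under moderate dependence and 33-47% under strong dependence, and a joint model avoids this when data are missing at random. If leaving depends only on the predictor in the model, there is no bias and the gain is roughly 3-10% in standard error. All these sizes rest on an assumed dropout mechanism, between-visit correlation and equal between-visit correlations in the simulated data; the article fixes none of them. That a missed visit simply falls out of its regression is an inference from ordinary linear regression, not a stated rule.

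**What to change.** In Data Analysis, replace the three separate linear regressions per predictor and continuous outcome with one linear mixed (repeated-measures) model using all available visits, with terms for visit, predictor and predictor-by-visit.

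- Report the three visit-specific slopes as the main results, with a visit-averaged slope only as a supplement.
- Report deaths before each visit separately. State that the model assumes missing at random among living participants and does not resolve outcomes undefined after death.
- If binary decline is also modelled jointly, use a likelihood-based mixed logistic model or weighted GEE, as a sensitivity analysis.

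Each model still has one predictor of interest, so the screening design is kept. The cost is analysis wording only, with no new data. The downside is a correlation assumption and slightly more complex models.
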